**Methods:**

The cross-sectional study design will recruit 378 patients with CHD (≥65 years) from Xiyuan Hospital of China Academy of Chinese Medical Sciences. The subjects' cognitive function is evaluated with MoCA scale, and they are divided into cognitive impairment group and normal cognitive function group according to the score results. Demographic data, disease characteristics (results of coronary CT/ angiography, number of stents implanted, status of diseased vessels), laboratory tests (biochemistry, coagulation, serum iron levels, pulse wave velocity), metabolites (blood samples and intestinal metabolites), and lifestyle (smoking, alcohol consumption, sleep, physical activity) will be assessed as outcome indicators. Compare the two groups and the correlation analysis will be performed on the development of mild cognitive impairment. Mann-Whitney U or X^2^ test was selected to describe and evaluate the variation, and logistics regression analysis was employed to fit the prediction model. After that, do the calibration curve and decision curve to evaluate the model. The prediction model will be validated by a validation set.

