#### 2.4.4. Laboratory indicators

Laboratory examination can accept the test results within 7 days before and after screening. It mainly includes the following contents: fasting glucose, glycosylated hemoglobin (HbA1c), total cholesterol, triglyceride, low-density lipoprotein, high-density lipoprotein, total bilirubin, serum creatinine, serum iron level (Fe), coagulation function (PT, APTT, TT, FIB), vascular ultrasound pulse wave velocity (PWV).

In addition to the above-mentioned indexes, in the early morning of the 2nd day after the selection, two tubes of peripheral venous blood of 5 ml will be drawn from a qualified phlebotomist and placed in the EDTA anticoagulant tubes. Centrifuge the blood samples (3,000 rpm at 4°C for 15 min), store them at −80°C, and then conduct untargeted metabolomics detection. 2 g of fresh fecal samples will be collected and put into aseptic collection tube and stored at −80°C immediately for metabolic detection and analysis of intestinal flora.

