### 2.6. Statistical analysis

Among the outcomes of this study, the measurement data in accordance with normal distribution are expressed by mean ± standard deviation, and independent sample *t*-test is used for comparison between the two groups. The measurement data that don't conform to the normal distribution are expressed in the median (quartile), and the Mann-Whitney U test is used for comparison between the two groups. Counting data were expressed as frequency or percentage, and X^2^ test was used to compare the two groups. Single factor analysis shall be conducted for all factors. In order to avoid the omission of important variables, the covariates with P <0.1 in the univariate analysis will be included in the multivariate logistic regression analysis. Stepwise forward regression analysis is used to analyze the independent risk factors of cognitive impairment in patients with CHD, and the OR value and 95% CI of each related factor will be estimated. The risk prediction model of cognitive impairment in patients with CHD would be established by adding independent risk factors. ROC curve will be drawn and the area under the curve (AUC) will be calculated to evaluate the effectiveness of the prediction model. Use Bootstrapping method to verify the accuracy of the final model internally. All tests with P<0.05 on both sides indicate that the difference is statistically significant, and other statistical analysis can be carried out by SPSS25.0.

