## 3. Discussion

Age-related cognitive decline is a series of natural cognitive changes that may develop into MCI or dementia. MCI is a state of cognitive impairment between healthy aging and dementia, which is considered as the prophase of dementia (25). But at this stage, the function of daily life remains basically intact. Delaying the onset of cognitive decline is the optimal strategy but where there are some earlier measures to slow the decline is important. Through comparative analysis of the population characteristics of the two groups, our study will screen out the specific markers of cognitive impairment in patients with CHD. So as to provide reference for early clinical identification and intervention of the disease.

The objective of this study is to ascertain the relationship between CHD and its risk factors and cognitive impairment in the elderly. At the same time, establish the risk prediction model of cognitive impairment in patients with CHD. The study will make available data regards CHD and MCI risk prediction. We propose leveraging the progress of machine learning to systematically compare different modeling approaches (26) to develop predictive tools for cognitive impairment in patients with CHD and verify their effectiveness. Comprehensive application of clinical observation, multi-source data processing, machine learning and other methods is also the innovation of the study.

Still, this research is subject to certain limitations. As an observational study, cross-sectional design has limitations e.g., causality cannot be inferred, we can only address the association. However, we try to include more observation factors, which are widely related to basic demographic data, disease characteristics, blood chemistry, metabolites and lifestyle. It is expected that some risk factors with clinical value can be found on the basis of this exploratory analysis. In order to broaden the current knowledge on CHD and its relationship with cognitive impairment in the elderly. Additionally, it will serve as a valuable foundation for hypothesis generation for future longitudinal studies and / or randomized controlled trials. In the future, it is necessary to conduct a larger sample of prospective cohort studies and add follow-up time to determine the incidence of secondary MCI in patients with CHD.

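### Read literally, Section 2.6 puts an unstated number of metabolomic features under the same uncorrected P<0.05 tests and P<0.1 model-entry rule as the clinical factors

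*Protocol article*

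**What the plan says.** Section 2.6 of the protocol article sets one analysis path and gives it universal scope:

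- Testing: "Single factor analysis shall be conducted for all factors".
- Entry to the model: "the covariates with P <0.1 in the univariate analysis will be included in the multivariate logistic regression analysis".
- Selection: "Stepwise forward regression analysis is used to analyze the independent risk factors of cognitive impairment in patients with CHD". The stepwise entry level is not given.
- Significance: "All tests with P<0.05 on both sides indicate that the difference is statistically significant".
- Internal validation: a bootstrap of the final model. Repeating the selection in each resample is not mentioned.

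Metabolites are placed inside that scope. The Methods part of the Abstract has "metabolites (blood samples and intestinal metabolites), and lifestyle (smoking, alcohol consumption, sleep, physical activity) will be assessed as outcome indicators", in a study that compares two groups. The Discussion describes the observation factors as "widely related to basic demographic data, disease characteristics, blood chemistry, metabolites and lifestyle". Section 2.4.4 says that the stored blood will be processed, "and then conduct untargeted metabolomics detection", and that faecal samples will be used for metabolic detection and flora analysis. The number of features is not stated for any of these assays.

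Section 2.3 bases the sample size on 18 independent variables, which it says are detailed in the outcomes part. They are not enumerated there as a list of 18.

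**The concern.** An untargeted assay reports whatever it detects, so its feature count is not fixed by the investigators and can be far above 18. A per-test level of 0.05 without correction produces false positives in proportion to that count. A P<0.1 screen passes twice as many null features into model selection. Forward selection then picks those that fit this sample best, and a bootstrap that holds the selected variables fixed does not see the selection step.

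Both deliverables are exposed. Chance differences could be reported as markers of cognitive impairment, and the AUC of the prediction model could be too high even after internal validation. The point concerns a rule that the article states. It is not a complaint that omics detail is missing.

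**Working it through.** **The plan's own figure.** Section 2.3 uses 18 variables, 5 to 10 subjects per variable and a 5% allowance.

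- 18 × 5 = 90 and 18 × 10 = 180, as stated.
- 2 groups × 180 × 1.05 = 378, as stated. The doubling is inferred from the reference to the two groups.
- Analysable subjects: 2 × 180 = 360. With 42.4% impaired (Section 2.3), 0.424 × 360 = 152.6, so about 153 cases, or 152.6 / 18 = 8.5 per variable.
- By the article's own rule, 360 subjects support 360 / 10 = 36 variables, or at most 360 / 5 = 72.

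The sample size reproduces from 18 variables and shows no allowance for omics features.

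**Expected false results.** Let m be the number of null features. m is an assumption, shown as a range because the article gives none. Expected false significant results are m × 0.05, and expected passes at the entry screen are m × 0.1. For m = 500, these are 500 × 0.05 = 25 and 500 × 0.1 = 50. Both expectations hold whether or not the features are correlated.

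**Effect on the model.** The rule was simulated with:

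- 360 subjects, 42.4% impaired, and independent normal features unrelated to the outcome;
- a t-test screen at P<0.1, then forward logistic selection by score test at P<0.05 (the entry level is an assumption);
- AUC in the development data and in 2,000 new subjects;
- a bootstrap with the selected variables held fixed.

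The number of simulated datasets fell from 100 at m = 100 to 8 at m = 2,000, so the last digit is approximate.

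| Null features | Expected P<0.05 | Expected P<0.1 | Mean number selected | Apparent AUC | Bootstrap AUC, selection fixed | AUC in new subjects |
|---|---|---|---|---|---|---|
| 100 | 5 | 10 | 4.8 | 0.65 | 0.63 | 0.50 |
| 200 | 10 | 20 | 10.3 | 0.73 | 0.69 | 0.50 |
| 500 | 25 | 50 | 22 | 0.84 | 0.80 | 0.50 |
| 1,000 | 50 | 100 | 41 | 0.94 | 0.90 | 0.50 |
| 2,000 | 100 | 200 | 71 | 1.00 (separation in every run) | not estimable | 0.50 |

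For comparison, 18 null variables give 18 × 0.05 = 0.9 false significant results and an apparent AUC of 0.55. The same rule does modest harm at the planned size and much more when applied to an omics platform.

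**What the fixed-selection bootstrap removes.** At m = 500 the optimism is 0.84 − 0.50 = 0.34, and the bootstrap takes off 0.84 − 0.80 = 0.04. At m = 1,000 the optimism is 0.44, and it again takes off 0.04.

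**The case against.** The strongest reply is that the article never says that individual omics features enter the logistic model. An 18-variable plan is hard to square with hundreds of candidates. Section 2.4.4 introduces the omics samples as an addition to the listed laboratory indicators, and the Discussion mentions machine learning, which leaves another path open. The Discussion also calls the work exploratory, and the Abstract promises a validation set. A fuller protocol or analysis plan may set out the omics analysis.

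Some of this stands. Entry of single features into the model is the literal reading and not the only possible one. Flora is named only in Section 2.4.4, and only the blood assay is called untargeted. The Discussion's promise of specific markers refers to a comparison of population characteristics and does not name metabolites.

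The rest does not remove the point. The Abstract and the Discussion list metabolites among what is compared, and Section 2.6 exempts nothing, so a separate plan with error control for omics would have to depart from its wording. An exploratory label does not make an uncorrected 0.05 a sound threshold for calling many features significant. The machine-learning remark does not limit the rule. The validation set is mentioned only in the Abstract and is not described. If it is truly independent it would expose an optimistic model, but it would not protect significance claims for single features.

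A reader might go further and infer that the plan will yield dozens of false markers and a near-perfect but worthless model. The documents do not support that. Dozens (24 or more) need about 24 / 0.05 = 480 null features, and a near-perfect AUC needs about 1,000 to 2,000. No count is given. A worthless model also requires that no clinical factor carries signal, whereas the article cites established associations for several.

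**Conclusion.** The concern holds in a conditional form. The wording of Section 2.6 is too broad for a study that includes untargeted metabolomics, and its planned bootstrap, if selection is held fixed, would hide most of the resulting optimism.

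The size depends on the feature count. It runs from 5 expected false significant features and an apparent AUC near 0.65 at 100 features to 50 and about 0.94 at 1,000. The false-positive counts assume that every feature is null. The AUC figures also assume independent features and a stepwise entry level of 0.05. Correlation between features would leave the expected counts unchanged but can lower the apparent AUC, and real signals would give the model some validity. The AUC figures are therefore a worst case and not a forecast. They apply only if omics features are in fact put through the stated rule, which the article should settle either way.

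**What to change.** Amend Section 2.6 in three respects:

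1. Limit the P<0.05 and P<0.1 rules to the 18 planned clinical factors, listed by name.
2. Analyse metabolite and flora features as a separate exploratory family with false-discovery-rate control, for example Benjamini-Hochberg.
3. If any omics information enters a prediction model, repeat the whole selection, screening included, inside each bootstrap resample.

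The change should be made before feature data are compared between the groups, so that results cannot drive the choice of correction. It costs about a paragraph of text and some extra computation, with no new patients, samples or procedures. The downside is that fewer metabolites will be called significant and the reported AUC will be lower.

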### 2.7. Data management

In this study, standardized case report form (CRF) tables will be used to collect data. Each participant will be assigned a unique identifier with the hospitalization number or patient ID code. Medical and other records of the participants will be kept by the researchers. EpiData3.1 software will be used for data entry and establishing the database. Once the data input is completed, the integrity and reasonableness of all data will be evaluated and checked by the researchers item by item. Check the problem with the original survey data and correct it after confirmation.

## 3. Discussion

Age-related cognitive decline is a series of natural cognitive changes that may develop into MCI or dementia. MCI is a state of cognitive impairment between healthy aging and dementia, which is considered as the prophase of dementia (25). But at this stage, the function of daily life remains basically intact. Delaying the onset of cognitive decline is the optimal strategy but where there are some earlier measures to slow the decline is important. Through comparative analysis of the population characteristics of the two groups, our study will screen out the specific markers of cognitive impairment in patients with CHD. So as to provide reference for early clinical identification and intervention of the disease.

The objective of this study is to ascertain the relationship between CHD and its risk factors and cognitive impairment in the elderly. At the same time, establish the risk prediction model of cognitive impairment in patients with CHD. The study will make available data regards CHD and MCI risk prediction. We propose leveraging the progress of machine learning to systematically compare different modeling approaches (26) to develop predictive tools for cognitive impairment in patients with CHD and verify their effectiveness. Comprehensive application of clinical observation, multi-source data processing, machine learning and other methods is also the innovation of the study.

Still, this research is subject to certain limitations. As an observational study, cross-sectional design has limitations e.g., causality cannot be inferred, we can only address the association. However, we try to include more observation factors, which are widely related to basic demographic data, disease characteristics, blood chemistry, metabolites and lifestyle. It is expected that some risk factors with clinical value can be found on the basis of this exploratory analysis. In order to broaden the current knowledge on CHD and its relationship with cognitive impairment in the elderly. Additionally, it will serve as a valuable foundation for hypothesis generation for future longitudinal studies and / or randomized controlled trials. In the future, it is necessary to conduct a larger sample of prospective cohort studies and add follow-up time to determine the incidence of secondary MCI in patients with CHD.

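### Age is controlled only if stepwise selection happens to keep it, so markers named from the unadjusted two-group tests may be markers of older age rather than of MCI

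*Protocol article*

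**What the plan says.** **Groups.** Section 2.1 divides patients by MCI status and states no matching or stratification by age. Table 1 admits anyone aged 65 or over, with no upper limit.

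**Two-group tests.** Section 2.6 applies covariate-free tests to the study's outcomes: "independent sample *t*-test is used for comparison between the two groups" for normal data, "the Mann-Whitney U test is used for comparison between the two groups" for non-normal data, and chi-square for counts. The scope is wide, "Single factor analysis shall be conducted for all factors", and one significance rule covers everything: "All tests with P<0.05 on both sides indicate that the difference is statistically significant".

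**Multivariable step.** Section 2.6 then states that "the covariates with P <0.1 in the univariate analysis will be included in the multivariate logistic regression analysis", and that "Stepwise forward regression analysis is used to analyze the independent risk factors of cognitive impairment in patients with CHD". Age, gender and education are collected (section 2.4.1), so they are candidates. None is named as a fixed term.

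**Metabolites and stool.** Section 2.4.4 plans untargeted metabolomics on blood and metabolic and flora analysis on stool. The Methods paragraph of the Abstract lists metabolites among the outcome indicators.

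**Use of the comparison.** The end of the Introduction states the aim as examining differences between the two groups, with the prediction model as a parallel aim. The Discussion says "Through comparative analysis of the population characteristics of the two groups, our study will screen out the specific markers of cognitive impairment", and opens with "Age-related cognitive decline is a series of natural cognitive changes that may develop into MCI or dementia".

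**The concern.** If cognitive decline goes with age, as the article says, an unmatched MCI group is likely to be older than the normal group. Any measure that changes with age then differs between the groups even if it has no relation to cognition among people of the same age. Pulse wave velocity, creatinine or a metabolite could qualify.

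This is confounding. A multiplicity correction does not remove it, because the difference between the groups is real and only its explanation is wrong. A larger sample makes it more significant.

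At stake is which measures the study puts forward as markers for early identification of MCI in CHD patients. The exposure is greatest for the metabolite and stool features, because the only comparison described in 2.6 that could take them one by one is the unadjusted one.

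**Working it through.** **Inputs from the article.** 18 independent variables, 5 to 10 patients per variable, 5% allowance, total 378 and 42.4% with cognitive impairment (section 2.3); tests, screen and selection rule (section 2.6).

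**Inputs assumed.** The article gives neither the age gap between groups nor the correlation of any marker with age. The age gap d is taken as 0 to 0.8 SD and the correlation r as 0.2 to 0.5. Stepwise entry at 0.05 and removal at 0.10 are also assumed.

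**Step 1, the plan's own figure.** 18 × 5 = 90 and 18 × 10 = 180. Reading 180 as per group, 180 × 2 = 360 and 360 × 1.05 = 378, as stated. The doubling is inferred from the reference to two groups. At 42.4%, 0.424 × 378 = 160 MCI patients and 218 normal.

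**Step 2, unadjusted test.** Let marker = r × age + √(1 − r²) × noise, with age shifted by d SD in the MCI group and within-group SD equal to 1. The marker has no link to MCI at a given age, yet its group means differ by r × d. The standard error is √(1/160 + 1/218) = 0.1041. The chance of P<0.05 is Φ(rd/0.1041 − 1.96) + Φ(−rd/0.1041 − 1.96).

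- d = 0.5, r = 0.3: 0.15/0.1041 = 1.44, giving 30.2% (simulated 30.0%).
- d = 0.5, r = 0.5: 0.25/0.1041 = 2.40, giving 67.1% (simulated 65.8%).

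With 359 patients left after 5% loss (378 × 0.95), simulation gives 29% and 65%.

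**Step 3, three routes compared.** Simulation with 378 patients, one marker plus age, 2,000 runs per setting. Entries are the percentage of runs in which the age-only marker is declared.

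| d | r | Unadjusted test | Screen, then stepwise | Age forced in |
|---|---|---|---|---|
| 0.2 | 0.2 | 6.0 | 4.2 | 4.7 |
| 0.2 | 0.5 | 15.6 | 6.0 | 4.2 |
| 0.3 | 0.3 | 12.8 | 3.4 | 4.3 |
| 0.3 | 0.5 | 29.9 | 6.2 | 5.3 |
| 0.5 | 0.3 | 30.0 | 1.8 | 4.6 |
| 0.5 | 0.5 | 65.8 | 2.2 | 4.7 |
| 0.8 | 0.3 | 63.0 | 2.4 | 4.8 |
| 0.8 | 0.5 | 97.6 | 3.4 | 4.1 |

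With d = 0, all three routes stay between 4.5% and 5.8%. Age passes the P<0.1 screen in about 60% of runs at d = 0.2, about 90% at d = 0.3 and practically always from d = 0.5.

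**Step 4, many candidates.** As an upper case, take age plus 17 candidates that are all related to MCI only through age (359 patients, 400 runs per setting). Age was absent from the final model in 36–82% of runs at gaps of 0.2–0.3 SD and in 4–13% at 0.5 SD. At d = 0.3 and r = 0.5, at least one age-only candidate was retained in 60% of runs, against 35% with age forced in; the 35% is multiplicity, a separate matter. At d = 0.5 forcing age made little difference (33–34% against 30–34%).

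**Step 5, untargeted features.** The article gives no feature count, so no number of false markers can be calculated. A model sized for 18 variables cannot take all of them; for any feature judged by a two-group test alone, the unadjusted column applies.

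**The case against.** The strongest reply is that section 2.6 does not stop at the two-group tests. It uses them as a screen and names independent risk factors, with odds ratios and 95% confidence intervals, from a multivariable model in which age can compete. This largely stands. A reader might infer that age-related markers will be reported as markers of MCI generally, or that the multivariable step repairs nothing. The article does not support either reading: in Step 3 the plan's route holds the per-marker rate at 1.8–6.2%.

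Other points have weight:

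- The marker sentence is Discussion prose, and the same section limits the study to association and hypothesis generation. But the Introduction also states the aim as examining group differences, so the sentence does not stand alone.
- Section 2.6 does not mention metabolomics, and a separate analysis may exist in a fuller document. So it is an inference that the plain tests apply to metabolites. It rests on the Abstract listing metabolites as outcome indicators and on 2.6 applying its tests to the outcomes. The point is therefore conditional and is not a complaint that an omics plan is missing.
- For pure prediction, a marker that partly follows age is no error. That covers the prediction model but not the claim to find markers of cognitive impairment.
- The calculations concern age only. Education has support in the article, since section 2.2 adds a MoCA point for fewer than 12 years of schooling. Sex is a conventional addition with no separate calculation behind it.

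**Conclusion.** The point holds in a limited form. Age control is left to data-driven selection, and the plan allows markers to be named from tests with no age control.

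- **Measures judged by the unadjusted tests alone:** the false-marker rate may be far above 5%. It is about 30% at an age gap of 0.5 SD with correlation 0.3 and about 65% with correlation 0.5. Over gaps of 0.2–0.8 SD and correlations of 0.2–0.5 it runs from 6% to 98%.
- **Factors judged by the stepwise model:** the excess per marker is small. The largest in Step 3 is 1.8 points (6.0% against 4.2%, at a gap of 0.2 SD and correlation 0.5). Age can still drop out of the final model at modest gaps, so whether it is adjusted for is partly chance.

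The sizes rest on assumed age gaps and correlations, on the assumed entry and removal limits, and in Step 3 on a single marker plus age. If the groups turn out equal in age, there is no bias from age. The direction does not depend on these values: with any age gap, an unadjusted comparison favours measures that follow age.

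**What to change.** 1. In section 2.6, state that the t-test, Mann-Whitney U and chi-square comparisons are descriptive.
2. Force age, sex and education into the multivariable logistic model, instead of leaving them to the P<0.1 screen and forward selection.
3. Name a metabolite or stool marker only from a regression containing these three covariates: logistic for MCI on the feature, or linear for the feature on group.
4. In the Discussion, replace the claim to screen out specific markers with factors associated with MCI after adjustment for age, sex and education.

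**Cost.** This changes analysis wording only, because section 2.4.1 already collects all three covariates. The model gives up three degrees of freedom (more if education is entered in several categories), and fewer factors will reach significance. In Step 3, forcing age gave a false-marker rate of 4.1–5.3% in every setting.
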